# The protocol for the prehabilitation for thoracic surgery study: a randomized pragmatic trial comparing a short home-based multimodal program to aerobic training in patients undergoing video-assisted thoracoscopic surgery lobectomy

**DOI:** 10.1186/s13063-023-07220-4

**Published:** 2023-03-15

**Keywords:** Multimodal prehabilitation, Aerobic training, Video-assisted thoracoscopic surgeries, Lobectomy, Pragmatic trial, Functional capacity, 6-min walk distance

## Abstract

**Background:**

Prehabilitation has been shown to have a positive effect on the postoperative recovery of functional capacity in patients undergoing video-assisted thoracoscopic surgery (VATS) lobectomy. The optimal way to implement prehabilitation programs, such as the optimal forms of prehabilitation, duration, intensity, and methods to improve compliance, remained to be studied. This Prehabilitation for Thoracic Surgery Study will compare the effectiveness of multimodal and aerobic training-only programs in patients undergoing thoracoscopic lobectomy.

**Methods:**

This randomized pragmatic trial will be conducted in Peking Union Medical College Hospital (PUMCH) and include 100 patients who are eligible to undergo VATS lobectomy. Patients will be randomized to a multimodal or aerobic training group. Prehabilitation training guidance will be provided by a multidisciplinary care team. The patients in the multimodal group will perform aerobic exercises, resistance exercises, breathing exercises, psychological improvement strategies, and nutritional supplementation. Meanwhile, the patients in the aerobic group will conduct only aerobic exercises. The interventions will be home-based and supervised by medical providers. The patients will be followed up until 30 days after surgery to investigate whether the multimodal prehabilitation program differs from the aerobic training program in terms of the magnitude of improvement in functional capability pre- to postoperatively. The primary outcome will be the perioperative 6-min walk distance (6MWD). The secondary outcomes will include the postoperative pulmonary functional recovery status, health-related quality of life score, incidence of postoperative complications, and clinical outcomes.

**Discussion:**

Prehabilitation remains a relatively new approach that is not widely performed by thoracic surgery patients. The existing studies mainly focus on unimodal interventions. While multimodal prehabilitation strategies have been shown to be preferable to unimodal strategies in a few studies, the evidence remains scarce for thoracic surgery patients. The results of this study will contribute to the understanding of methods for thoracoscopic lobectomy patients.

**Trial registration:**

ClinicalTrials.gov NCT04049942. Registered on August 8, 2019.

**Supplementary Information:**

The online version contains supplementary material available at 10.1186/s13063-023-07220-4.

## Background

Lung cancer remains the leading cause of cancer-related deaths worldwide [1]. For localized non-small cell lung cancer (NSCLC), surgical resection with radical lymph node dissection is a potentially curative option [2]. Surgical techniques have advanced, and video-assisted thoracoscopic surgery (VATS) is currently a well-established and preferred choice at many institutions due to its minimally invasive nature [3]. However, the incidence of postoperative pulmonary complications (PPCs) is still reported to be 12–40% [4, 5].

The concept of prehabilitation, the process of optimizing the functional capacity of an individual before surgery, has been developed to improve the outcomes of surgical patients [6]. Although various unimodal and multimodal prehabilitation strategies have been shown to improve functional capacity in patients undergoing gastrointestinal surgeries [6–11], pursuing an optimal strategy remains a work in progress, especially in the thoracic surgery community.

Until recently, most of the preoperative interventions that have been implemented in thoracic surgery patients have been unimodal, and the majority of previous studies have focused on exercise-based training programs, particularly aerobic exercises [12–14]. Although there is increasing evidence that preoperative exercise training improves physical function and pulmonary function, it remains unclear how exercise training compares to other forms of prehabilitation in efficacy and whether improvements in functional capacity lead to better postoperative outcomes.

Our team conducted a randomized controlled trial in 2017 (registration number NCT03068507) to examine the efficacy of a 2-week multimodal home-based prehabilitation strategy in patients undergoing thoracoscopic surgeries for lung cancer. The multimodal program included physical exercise, respiratory training, nutritional supplements, and psychological optimization. This study yielded promising results, showing that a short-term home-based multimodal prehabilitation program could improve perioperative functional capacity in patients undergoing thoracoscopic lobectomy, as indicated by an improved perioperative 6-min walk distance (6MWD) [15]. The average 6MWD was 60.9 m higher perioperatively in the prehabilitation group compared to the control group (95% confidence interval [CI], 32.4–89.5; *P* < 0.001).

The Prehabilitation for Thoracic Surgery Study aims to further understand the role of prehabilitation in thoracoscopic surgery patients by comparing the efficacy of a short multimodal home-based prehabilitation program with an aerobic exercise-only prehabilitation program, as the latter has been most extensively investigated to date.

### Research question

The aim of the Prehabilitation for Thoracic Surgery Study is to answer the following question: Is short-term multimodal prehabilitation more beneficial than aerobic exercise-based prehabilitation in improving perioperative functional walking capacity in patients undergoing VATS lobectomy?

## Methods

### Trial design

The Prehabilitation for Thoracic Surgery Study is a randomized pragmatic trial comparing the impact of a short home-based multimodal prehabilitation program to a preoperative aerobic training program in patients undergoing VATS for lung cancer. The overall trial design is illustrated in Fig. 1 (see Additional file 1 for the Standard Protocol Items: Recommendations for Interventional Trials (SPIRIT) Checklist). Ethics board approval of this study was obtained from the Peking Union Medical College Hospital (PUMCH) Institutional Review Board on July 23, 2019. This study will be conducted in PUMCH by a multidisciplinary care team, including anesthesiologists, thoracic surgeons, nutritionists, and rehabilitation medicine practitioners. After they are recruited and provided consent, the patients will be randomized to two study arms; then, they will be instructed to undergo either a tailored aerobic program or a multimodal prehabilitation program during the period of time prior to surgery. The patients will have a 30-day follow-up after surgery. The effects of the two arms will be assessed on the basis of physical capacity test results (6MWD), pulmonary function test results, patient-reported qualitative outcomes, clinical outcomes, and perioperative laboratory results. The patients, care providers, and researchers in charge of enrolling, following up, and assessing outcomes (performing the 6MWT) will not be blinded to the allocation due to the nature of the intervention. Data analysts will be blinded. Generally, data analysts will not need to be unblinded.

**Fig. 1 Fig1:**
[figure not shown]
Flow diagram of the study. 6MWT, 6-min walk test; PFT, pulmonary function test; HADS, Hospital Anxiety and Depression Scale; WHODAS 2.0, World Health Organization Disability Assessment Schedule II; Borg RPE, Borg Rating of Perceived Exertion Scale; POD, postoperative day; QoR-15, Quality of Recovery Score-15

### Participant eligibility criteria

The participating patients must be (1) thoracic surgery outpatients in PUMCH, (2) aged from 18 to 70 years, (3) suspected of having lung cancer, and (4) scheduled for elective thoracoscopic surgery in PUMCH. Patients will be excluded from the study if they (1) decline to participate in the study (due to any reason), (2) have an American Society of Anesthesiologists (ASA) grade > III, (3) plan to undergo or have undergone neoadjuvant therapy, (4) are unable to tolerate any component of the multimodal prehabilitation or aerobic program (including exercises, whey protein supplements, and functional capacity tests), or (5) have other severe cardiopulmonary diseases that may affect the 6MWD results.

### Patient recruitment and allocation

In PUMCH, approximately 100–150 VATS lobectomy surgeries are scheduled each month. Patients will be recruited from the thoracic surgery outpatient department where they receive consults before surgery. When they are scheduled for VATS lobectomy, they will be screened for eligibility and asked to provide informed consent by a research staff. The patients included will then be randomly assigned to two equally sized groups, the multimodal prehabilitation group and the aerobic prehabilitation group, on the basis of a computer-generated sequence. The random allocation results will be concealed using sealed opaque envelopes. One of the main researchers of the study designs the statistical analysis plans and will be generating the allocation sequence. Two experienced anesthesiologist researchers will be in charge of enrolling and assigning participants according to the randomization result.

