### Oversight and monitoring

The Project Manage Group consists of two main researchers who are experienced anesthesiologist researchers. They will meet with other team members every 2 weeks to oversee work in various phases, discussing problems met during recruitment and follow-up. All research investigators comprise the Trial Steering Committee, and they will meet every half year to supervise the research progress and discuss if there is a need to make amendments to the protocol. The Ethics Committee and sponsor hold auditing every year to review conduct.

The DMC members will monitor the integrity of the data and patient safety. Upon data entry, the database will be locked by a password. DMC members will make the decision to unblind, conduct an interim analysis, or terminate the trial, if they deem it necessary. The DMC members meet every month to discuss exercise injuries and other safety risks.

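### The protocol's description of roles suggests that the researcher who generates the allocation sequence is one of the two who enrol and assign, so allocation concealment is not assured

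*Protocol article*

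**What the plan says.** Four statements in the protocol article bear on this.

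- **Who makes the list** (Patient recruitment and allocation): "One of the main researchers of the study designs the statistical analysis plans and will be generating the allocation sequence".
- **Who enrols and assigns** (same section, next sentence): "Two experienced anesthesiologist researchers will be in charge of enrolling and assigning participants according to the randomization result".
- **Who the main researchers are** (Oversight and monitoring): "The Project Manage Group consists of two main researchers who are experienced anesthesiologist researchers".
- **How allocation is hidden** (Patient recruitment and allocation): "The random allocation results will be concealed using sealed opaque envelopes".

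On blinding, the trial design section says that patients, care providers and the researchers who enrol, follow up and perform the walk test "will not be blinded to the allocation due to the nature of the intervention". For the analysis it says: "Data analysts will be blinded. Generally, data analysts will not need to be unblinded". It does not identify the analysts. The dissemination section gives the main researchers full access to the final dataset.

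**The concern.** Concealment works when the person deciding whether and when a patient enters the trial cannot know the next assignment. Envelopes achieve this only for people who have not seen the list. The text points to a list-maker who also enrols, and it nowhere says that the two tasks are kept apart.

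Several features make this matter more here than in many trials:

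- Nobody who enrols, treats or measures is blinded, so concealment before assignment carries most of the protection against selection.
- The hospital schedules about 100 to 150 of these operations a month, and the trial needs 100 patients in total. There is wide room to choose whom to approach and when.
- One exclusion criterion, inability to tolerate a component of either program, calls for judgement.
- The baseline interview, including the baseline walk test, takes place after allocation and is done by unblinded staff. Adjustment for baseline imbalance would use a measurement made with the arm known, and it cannot capture unmeasured motivation.

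At stake is a multimodal arm filled, knowingly or not, with patients expected to do better. No later analysis could fully undo that.

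**Working it through.** The point concerns roles, so the check is mainly a comparison of texts. A short calculation illustrates scale.

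**Step 1. Compare the descriptions.**

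| Role | Number | Description | Source |
|---|---|---|---|
| Generates the sequence, designs the analysis plan | one | a main researcher | Patient recruitment and allocation |
| Enrols and assigns | two | experienced anesthesiologist researchers | Patient recruitment and allocation |
| Project management group | two | main researchers, who are experienced anesthesiologist researchers | Oversight and monitoring |

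The third row links the first two: it shares its title with row one, and its number and professional description with row two. The most direct reading is that rows two and three are the same pair and that row one is a member of it.

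**Step 2. Test whether that reading is forced.** It is not. No sentence says that the list-maker enrols. The oversight section does not say that its two members are the only main researchers or the only researchers fitting that description. Nor does any sentence say that the roles are held by different people. The overlap is suggested, not stated.

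**Step 3. Consequence if the overlap is real.** The list-maker can know upcoming assignments. Sealed opaque envelopes are the only concealment device named, and they do not bind that person.

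**Step 4. Consequence for analysis.** The list-maker designs the analysis plan. Designing a plan is not running the analysis, and access to the final dataset is not the analyst's role. The statement "Data analysts will be blinded" is not contradicted anywhere.

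**Step 5. Illustration of scale.** Inputs from the sample size section: SD 50 m, 45 evaluable patients per group, two-sided 5% level. Assumed, with no source in the document: a false arm difference d at day 30 caused by selection alone.

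- Standard error = 50 × √(2/45) = 10.54 m
- Degrees of freedom = 2 × 45 − 2 = 88; critical t = 1.987
- Noncentrality = d / 10.54
- False-positive rate = P(|T| > 1.987), with T noncentral t on 88 degrees of freedom

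| Assumed shift d | Noncentrality | False-positive rate |
|---|---|---|
| 0 m | 0 | 5.0% |
| 5 m | 0.474 | 7.6% |
| 10 m | 0.949 | 15.5% |
| 15 m | 1.423 | 29.1% |

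The 10 m row is one third of the 30 m target difference. The table describes a t-test at day 30, not the planned linear mixed model for the intervention-by-time interaction.

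**The case against.** The strongest reply is that the overlap is read into the text. Consecutive sentences in the allocation section use different labels for the list-maker and the enrollers, which could itself signal separation. Similar wording does not identify people in this document: the data collection section describes two experienced anesthesiology doctors on the data monitoring committee who are declared independent of the study. A fuller division of roles may also sit in protocol version 2.1, which is not shown. This stands to the extent that the overlap must be put conditionally. It does not remove the point, because the article states who does what and its statements point towards overlap.

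A second reply is that a member of the research staff screens and seeks consent before assignment. That weakens the route to selective entry but does not close it, because the two anesthesiologists are in charge of enrolment.

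A third reply is that a stable difference in fitness, present at baseline, would largely cancel in the interaction test. This is right and limits what the 15.5% can show. Selection on expected change, through motivation for example, would remain.

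A reader might also infer that concealment has failed, or that analyst blinding fails because the list-maker designs the analysis. The document supports neither. The first depends on an overlap that is not stated. The second confuses writing the plan with analysing the data, and the protocol says that analysts are blinded.

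**Conclusion.** The point holds in conditional form. The protocol's own descriptions suggest that the sequence generator is one of the two people who enrol and assign. If that is so, the envelopes do not conceal the sequence from that person, and the trial lacks its main defence against selection. If it is not so, the two sections are worded misleadingly and need correcting. Either way the text should change.

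The size of any bias cannot be estimated from the document. The figures of 7.6%, 15.5% and 29.1% rest on assumed shifts of 5, 10 and 15 m and on a simpler test than the one planned, so they show only that a modest shift would matter. There is no finding against the blinding of the analysts. This is a change that should be made, since it is cheap and, at publication in March 2023, recruitment was expected to run until November 2023.

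**What to change.** For the remaining allocations, have a person with no part in enrolment, assignment, outcome assessment or analysis generate and hold the sequence and prepare sequentially numbered sealed opaque envelopes. A statistician in the hospital's Medical Research Center would serve, such as the one already on the data monitoring committee. If giving that member an operational task is thought to compromise the committee's independence, another statistician in that department would do.

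Add two statements to the protocol: that no one who enrols or assigns has access to the sequence, and that whoever generated the list used so far is not the blinded analyst. If the roles are already held by different people, correct the sections on patient recruitment and allocation and on oversight and monitoring to say so; the reassignment is then unnecessary.

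The cost is a short amendment and the transfer of one task, without new staff if an existing statistician takes it on. Allocations already made stay as they are, so the change cannot protect patients enrolled under the present arrangement. The trial report should therefore say who generated the list and who enrolled in each period.

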### Baseline interview

Upon patient recruitment and allocation to groups, a one-on-one baseline interview and evaluation will be conducted to (1) record patients’ comprehensive medical history; (2) assess patients’ nutritional states; (3) assess patients’ functional capacity during the 6-min walk test (6MWT); (4) conduct a pulmonary function test (Spirodoc portable pulmonary function meter, Medical International Research S.r.l., 09,000,261,972), during which the forced expiratory volume in 1 s (FEV1, L), FEV1%, forced vital capacity (FVC, L), FVC%, FEV1/FVC, peak expiratory flow (PEF, L/s), and PEF% will be recorded; (5) record laboratory results, if applicable, including the levels of alanine transaminase (ALT), creatine (CR), C-reactive protein (CRP), albumin (Alb), glucose (Glu), and myocardial enzymes; (6) evaluate the patients’ baseline quality of life and mental state using standard tools [hospital anxiety and depression scale (HADS), World Health Organization disability assessment schedule II (WHODAS 2.0) score, postoperative quality of recovery score-15 (QoR-15)]; (7) explain in detail the prehabilitation plan for both groups; and (8) encourage patients to choose a preferred way to be followed up, such as by telephone, short text messages, or WeChat messaging.

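### Baseline 6MWT, spirometry, HADS and WHODAS 2.0 are scheduled after open allocation, so these baselines can differ by arm because of the allocation and carry that difference into the intervention-by-time analysis

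*Protocol article*

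**What the plan says.** The order of events is given in three sections of the protocol article, and they agree.

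- **Patient recruitment and allocation:** when patients are scheduled for surgery, "they will be screened for eligibility and asked to provide informed consent by a research staff". Those included are then randomised to two equal groups, with the sequence concealed in sealed opaque envelopes.
- **Trial design:** "After they are recruited and provided consent, the patients will be randomized to two study arms; then, they will be instructed to undergo" one of the two programs.
- **Baseline interview:** "Upon patient recruitment and allocation to groups, a one-on-one baseline interview and evaluation will be conducted to" carry out a list of tasks. Item 3 is the 6MWT, item 4 spirometry, and item 6 is to "evaluate the patients’ baseline quality of life and mental state using standard tools" (HADS, WHODAS 2.0, QoR-15). Item 7 is the explanation of the prehabilitation plan.

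On blinding, Trial design says that the patients, the care providers and the "researchers in charge of enrolling, following up, and assessing outcomes (performing the 6MWT) will not be blinded to the allocation". Only the data analysts are blinded.

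Outcomes lists baseline as one of the three time points of the primary 6MWD outcome. Statistical analysis names a linear mixed-effects model with an intervention-by-time interaction for 6MWD, pulmonary function, HADS and WHODAS 2.0, and says that the primary analysis will be adjusted if there is evident baseline imbalance.

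**The concern.** A baseline value protects a comparison only if allocation cannot have affected it. Here the walk is taken, and the questionnaires answered, once the arm has been assigned and can be known to both patient and tester. Someone who has just drawn the fuller or the thinner program may walk or answer differently, and a tester who knows the arm may encourage differently. The baseline difference between arms is then no longer due to chance alone.

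The interaction model reads treatment effect partly as change from that baseline. If the multimodal arm underperforms at baseline, its benefit is exaggerated; if it overperforms, a real benefit is masked. Adjusting for the observed imbalance cannot separate chance from the effect of allocation.

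A second, weaker route concerns eligibility. One exclusion covers patients who "are unable to tolerate any component of the multimodal prehabilitation or aerobic program (including exercises, whey protein supplements, and functional capacity tests". The first scheduled 6MWT is at the post-allocation interview, as is the physical evaluation that precedes resistance training (described under the multimodal strategy). Intolerance might therefore first come to light when the arm is known.

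**Working it through.** **Inputs from the document (Sample size):** SD of 6MWD 50 m in both groups; planning difference 30 m at 30 days; 45 patients per arm, 50 recruited; two-sided 5% level.

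**Inputs assumed, because the document gives neither:** a between-arm shift *b* in baseline effort of 5, 10 or 15 m, and a baseline-to-day-30 correlation *r* of 0.5 to 0.8. I also assume the same SD at both times, no true treatment effect, and a shift that affects baseline only.

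**The plan's own figure.** The document has none for this bias. Its 45 per arm is used here only as the analysed number. It does not reproduce at the stated 90% power (30 m and SD 50 m need 59 per arm; 45 gives about 80–81%), but that is a separate matter and does not affect this point.

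**Change-from-baseline contrast** (the baseline-to-day-30 part of the interaction):

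- bias = *b*
- SE = 50 × √(2(1 − *r*)) × √(2/45)
- at *r* = 0.5: 50 × 1 × 0.2108 = 10.54 m; at *r* = 0.8: 50 × 0.6325 × 0.2108 = 6.67 m

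**Baseline-adjusted contrast:**

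- bias = *r* × *b*
- SE = 50 × √(1 − *r*²) × √(2/45)
- at *r* = 0.5: 9.13 m; at *r* = 0.8: 6.32 m

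**Type I error** = Φ(−1.96 + bias/SE) + Φ(−1.96 − bias/SE). For *b* = 10 and *r* = 0.5, the change contrast has bias/SE = 10/10.54 = 0.949, giving 0.158.

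| *r* | Change contrast: 5 / 10 / 15 m | Baseline-adjusted: 5 / 10 / 15 m |
|---|---|---|
| 0.5 | 7.6% / 15.8% / 29.6% | 5.9% / 8.5% / 13.0% |
| 0.7 | 9.4% / 23.2% / 45.1% | 7.5% / 15.3% / 28.6% |
| 0.8 | 11.7% / 32.3% / 61.4% | 9.7% / 24.4% / 47.5% |

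Using the t distribution at *r* = 0.5, the change-contrast figures are 7.6%, 15.5% and 29.1%. With 50 per arm, a 10 m shift gives 17.0–35.3% (change) and 8.9–26.6% (adjusted). With *b* = 0 the error stays at 5%.

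**Would the conditional adjustment be triggered?** The SE of the baseline difference between arms is 50 × √(2/45) = 10.54 m. A 10 m shift is 10/10.54 = 0.95 of one SE, so it need not look like an evident imbalance. It is nevertheless 10/30, one third, of the planning difference.

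**The case against.** Several points on the other side are sound.

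- **Both arms are active.** They receive the same aerobic instructions and the same twice-weekly contacts, and the 6MWT follows ATS procedures with trained staff and standard wording. These features make a large shift less likely, but they do not exclude one.
- **The plan is explained at item 7, after the tests in the list.** A patient might not yet know the arm when walking. But the article does not say that allocation is withheld until then, and it states that the 6MWT staff are unblinded.
- **The figures rest on assumed shifts and correlations.** This stands. A reader might take 16–32% as this trial's actual error rate; the document does not support that, because neither the shift nor its direction is known.
- **Adjustment helps.** It does: at *r* = 0.5 it halves the bias. It does not remove it.

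Two stronger readings are tempting. One is that staff will exclude patients after allocation. No section provides for this: screening comes before randomisation, and intolerance during the study leads to discontinuing the intervention, not to removing the patient. Late exclusion is only a possibility.

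The other is that all results are affected. They are not. As an outcome, QoR-15 is postoperative, and together with length of stay, chest tube duration and complications it falls outside the interaction model. Laboratory values do not depend on effort. The presurgery-to-day-30 part of the interaction does not use baseline, and the sample size is set on the day-30 difference.

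**Conclusion.** The point holds for 6MWD (primary), spirometry, HADS and WHODAS 2.0. The stated procedure takes effort-dependent or self-reported baselines after open allocation and then uses them in the primary type of analysis. This opens a route to bias that the trial does not need: the article attributes the lack of blinding to the nature of the intervention, but nothing in the intervention requires the baseline tests to follow allocation.

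Size and direction cannot be derived from the document. Under the assumptions listed, a 10 m shift would raise a 5% error to about 16–32% for a change contrast and about 8.5–24% with baseline adjustment. Exclusions made after allocation remain a possibility that the text neither plans nor rules out.

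**What to change.** For every patient not yet randomised, complete consent, the eligibility check (including tolerance of the functional capacity tests) and all baseline tests and questionnaires first. Only then open the envelope and explain the allocated plan.

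For patients already enrolled:

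- keep everyone allocated in the analysis, if the full protocol or SAP does not already say so;
- report any post-allocation exclusions by arm, with reasons;
- add a sensitivity comparison of day-30 6MWD between arms that does not use baseline.

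The cost is a short procedural amendment; no additional test is needed. If allocation and interview now take place on different occasions, which the article does not say, the timing of allocation would have to move. The day-30 comparison is less precise: its SE is 50 × √(2/45) = 10.54 m, against 6.32–9.13 m for the adjusted contrast over the same range of *r*. It is therefore a check and not a replacement.

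Two limits remain. Recruitment began in November 2019 and was expected to end in November 2023, with the article published in March 2023, so many patients may already have a post-allocation baseline; a check confined to those enrolled after the change could rest on a small subset. Unblinded follow-up testing is also unchanged by this fix.
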